## 9. Statistical Procedures

### 9.1 Definition of Clinical Trial Population to be Analyzed

The **safety analysis set** (SAF) comprises all randomized patients and is identical with the **full analysis set** (FAS). The **per-protocol set** (PPS) comprises all patients of the FAS who followed treatment for at least 9 months and completed neuropsychologic testing (BSID-III) at 2 years. All patients of the PPS need to fulfil the inclusion criteria 1 and exclusion criteria 1 and 2. For efficacy analyses the patients will be analysed as allocated, for safety analyses as treated.

For the analyses “as treated”, participants randomized to the Sirolimus arm are regarded as treated according to standard of care only, if

- They are lost to follow-up before 6 months after randomization or
- They never started treatment

Participants randomized to the standard of care arm are regarded as treated with Sirolimus, if

- They received prophylactic mTOR inhibitor

Screening and disease characteristics will be analysed once by treatment groups as treated.

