## 5. Treatment

### 5.1 Measures to minimize Bias

#### 5.1.1 Randomization

Within -14 days prior to study visit V1 and the time of randomization, all required elements of the screening visit will be fully completed and documented by a qualified staff member. For this purpose, informed consent must be obtained from legal guardian(s). The diagnosis of TSC must be confirmed based on the diagnostic criteria. Inclusion criteria and exclusion criteria must be reviewed and documented. Vital signs, physical examination results, EEG, abdominal sonography, and laboratory results must be complete. The results will be entered by a qualified member of the local study team with access to the eCRF. Subsequently, after internal validation, randomization is performed directly via the eCRF at the site on visit 1 and treatment will start at the same day after calculation of the starting dose. The randomization via the eCRF will trigger an email to inform the sponsor and the delegated persons by the sponsor. Eligible patients will be randomized 1:1 to interventional and control arm. Block randomization will be used to minimize the imbalance between the number of patients in each treatment group. While we are expecting no centre effects due to the highly standardized therapeutic management of TSC patients, age at inclusion might bias results. Since the primary endpoint is assessed at two years of age and age at inclusion might vary from 0 to <4 months, the total treatment duration will be different depending on the age at inclusion. Therefore, the randomization will not be stratified by centre but by age groups (0-<2 vs. 2-<4 months of age).

Blinding procedures for the groups are not applicable.

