## 9.5 Secondary Analyses

### 9.5.1 Main Trial Analyses

**All secondary parameters** will be analyzed for the FAS.

BSID-III cognitive scale at the age of 1 year will be analysed similar to the primary endpoint. In addition, the BSID-III cognitive scale and important subscales will be analysed descriptively by group and time point using standard descriptive measures for continuous variables. The VABS total scales, important VABS subscales, ADOS total scales, and important ADOS subscales will be analysed descriptively by group and time point using standard descriptive measures for continuous variables, as well. In addition, for cognitive impairment and autism spectrum disorders at 1 and 2 years of age, 95% CIs will be calculated by treatment group in addition to the relative frequencies using the method of Wilson. The M-CHAT-R/F and TAND will be analysed descriptively by group and time point using absolute and relative frequencies.

The MRI characteristics (as defined in Section 6.8) will be analysed by group and time point, i.e. randomization (last image before randomization) and at 2 years of age  $\pm$  6 months.

Seizure characteristics, EEG characteristics, abdominal sonography characteristics, ECG and echocardiography characteristics (as defined in Section 6.8) will be analysed by treatment group and time point (if applicable).

All **safety parameters** will be analyzed for the SAF. Only treatment emergent-event adverse events will be analysed. Frequencies (number of adverse events & number and percentage of patients with at least one adverse event) will be tabulated according to system organ class and preferred term. One table each will be created showing: all adverse events, all serious adverse events, all adverse events of special interest, all non-serious adverse events, all adverse events leading to death, all adverse events related to the treatment (treated group only), all adverse events by severity. In addition, adverse events and special situations will be analysed by categories defined in the eCRF (number of events & number and percentage of patients with at least one event).

For laboratory values and vital signs, the analyses will be conducted by visit and shift tables comparing all values by visit to the relevant baseline value will be displayed additionally.

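### For safety, a sirolimus-arm child lost to follow-up before 6 months is counted as standard of care, even if the child was dosed from day 0

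*Protocol*

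**What the plan says.** Protocol section 9.1 makes the safety set all randomised patients and sets the grouping: "For efficacy analyses the patients will be analysed as allocated, for safety analyses as treated".

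It then defines treatment received. In its words, "participants randomized to the Sirolimus arm are regarded as treated according to standard of care only, if" one of two conditions is met, joined by 'or':
- "They are lost to follow-up before 6 months after randomization"
- "They never started treatment"

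The only rule for the control arm concerns children who received a prophylactic mTOR inhibitor. No condition moves a control child who is lost early.

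Other sections fix what follows from this:
- Section 5.1.1: "randomization is performed directly via the eCRF at the site on visit 1 and treatment will start at the same day", once the starting dose has been calculated.
- Section 7.3.2: loss to follow-up means that the child does not return and the caregivers cannot be reached. It says nothing about exposure.
- Section 9.2: an adverse event is treatment-emergent from randomisation onwards.
- Section 9.5.1: safety is tabulated on the safety set, and one of the tables is "all adverse events related to the treatment (treated group only").

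On baseline, section 9.1 states: "Screening and disease characteristics will be analysed once by treatment groups as treated".

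**The concern.** Grouping by treatment received is meant to place each child's events under the drug the child actually took. The loss-to-follow-up condition does the opposite. It uses a fact about follow-up to decide exposure, and it labels a dosed infant as undosed. The window covers the whole titration phase and the months just after it.

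Adverse events, serious adverse events and events of special interest are a listed secondary endpoint (section 2.2.1, item 9). With 30 children per arm, one or two moved cases can visibly change the table for an uncommon serious event. Because a moved child leaves the treated group, events judged related to sirolimus also drop out of the only table devoted to them.

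**Working it through.** **Reading the rule**

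1. A sirolimus-arm child who was never dosed is already covered by the second condition. The loss condition therefore adds only children who received sirolimus.
2. Dosing starts on the day of randomisation, so a child lost just before 6 months may have had almost 6 months of drug.
3. Events count from randomisation, and the safety set keeps every randomised child. Events recorded before loss therefore enter the tables, in the standard-of-care column.
4. Nothing elsewhere in the protocol adds an exposure condition or overrides the rule.

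The protocol gives no figure for the effect of this rule, so there is none to reproduce.

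**Inputs**

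- 30 children per arm (section 4.1).
- Number lost before 6 months in the sirolimus arm, k: not stated. Section 9.9 assumes 10% missing values for the 24-month endpoint, for any reason: 0.10 × 30 = 3. I use k = 0 to 3, with 3 as an upper illustration.
- Event counts and rates: my assumptions, shown below.

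**Case A: loss linked to events.** Assume 3 sirolimus children and no controls have an early serious event, and the k lost children are among those 3. The sirolimus column becomes (3 − k)/(30 − k) and the control column k/(30 + k).

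| k lost | Sirolimus as reported | Control as reported |
|---|---|---|
| 0 (truth) | 3/30 = 10.0% | 0/30 = 0% |
| 1 | 2/29 = 6.9% | 1/31 = 3.2% |
| 2 | 1/28 = 3.6% | 2/32 = 6.25% |
| 3 | 0/27 = 0% | 3/33 = 9.1% |

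With one child lost the difference shrinks but keeps its direction. With two or three it reverses.

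**Case B: loss unrelated to events.** Assume true event rates of 50% on sirolimus and 20% on control. The sirolimus rate stays at 50% on average. The control rate becomes (30 × 0.20 + k × 0.50)/(30 + k).

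- k = 1: (6 + 0.5)/31 = 21.0%, difference 29.0 points.
- k = 3: (6 + 1.5)/33 = 22.7%, difference 27.3 points instead of 30.0.

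**Case C: none of the lost children had the event.** With the same 3 affected children and k = 3, the report reads 3/27 = 11.1% against 0/33 = 0%, slightly above the true 10.0%. The direction of the error therefore depends on who is lost.

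**The case against.** The strongest case on the other side is that the rule is narrow and the tables are not the only safeguard. Much of this stands.

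- **Scope.** A reader might infer that early sirolimus toxicity in general is shown under control. The protocol does not support that. Intolerance normally leads to temporary or permanent discontinuation (sections 7.1 and 7.2), after which the child may remain in the trial and be followed. Withdrawal of consent (7.3.1) and death (7.3.3) are listed apart from loss to follow-up. Read literally, none of these children is moved, although section 9.1 does not say so explicitly.
- **Link between loss and toxicity.** A reader might also infer that early losses are mostly toxicity cases. Section 1.3.8 cites a chart review with 7 of 17 serious events in the first 3 months, but that is the timing of events, not of loss.
- **Size.** The 10% is all-cause missingness at 24 months, and section 9.9 also cites a 5% drop-out rate in another trial. Three children lost within 6 months, all affected, is the extreme of Case A.
- **Other safeguards.** Expedited reporting of serious events, second assessment, reporting of suspected unexpected serious reactions and the individual risk-benefit evaluations work case by case. All eCRF data are listed (section 9.3). The primary analysis is as allocated and is untouched.
- **Control children given an mTOR inhibitor.** It is tempting to add this to the same charge. Moving all of such a child's events to sirolimus would tend to count against sirolimus, and how to split event time is ordinary SAP detail.
- **Baseline.** To say that the randomised groups can never be compared would go too far: section 9.3 allows further analyses, and the two versions differ only by the few reclassified children.

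These points limit how many children are affected. None of them gives a reason for counting a dosed child as undosed.

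**Conclusion.** The rule is wrong as written, within a narrow scope. A sirolimus-arm child who was dosed and is then lost to follow-up before 6 months has on-drug events reported under standard of care and removed from the related-events table, with no matching rule for controls.

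The number moved is unknown and is probably 0 to 3 of 30. If losses are concentrated in affected children, a rare serious event can be diluted (1 lost) or shown on the wrong side (2 or 3 lost). If losses are unrelated to events, the distortion is modest: 30.0 to 27.3 points with 3 moved, at assumed rates of 50% and 20%. The documents do not support a claim that the safety comparison as a whole will be reversed, or that it must always favour sirolimus. Case-level safety reporting and the primary efficacy analysis are unaffected.

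A secondary and minor point is that section 9.1 has baseline characteristics analysed once, by treatment received, while efficacy is analysed as allocated. The one planned baseline table therefore need not match the groups that the primary analysis compares.

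**What to change.** - In section 9.1, delete the condition on loss to follow-up before 6 months.
- Define treatment received by exposure: any sirolimus-arm child with at least one dose is analysed under sirolimus for safety, and only never-dosed children are analysed as standard of care.
- As a minor addition, show screening and disease characteristics by allocated group.
- Leave to the SAP how event time is split for control children who receive an mTOR inhibitor.

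The cost is a few sentences. Section 9.3 allows changes outside the primary analysis to be made in the SAP alone. No extra data, visits or patients are needed.

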All infants with TSC have a relevant risk for additional manifestations of disease, which includes a very high risk for epilepsy up to 90% [18], being often refractory to treatment. Nearly all individuals with TSC also develop cerebral malformations (>90%) and cardiac rhabdomyoma (>90%) with a risk for arrhythmia and heart failure and about one quarter of individuals will develop SEGA during childhood. Half of affected individuals develop facial angiofibroma and renal angiomyolipoma until adolescence. All of these manifestations are associated with high morbidity and mortality (renal angiomyolipoma) and affect the quality of life of individuals with TSC [29], [5]. Overall, TSC-related morbidity from organ manifestations outside functional neurodevelopmental disorders is highly relevant. As mTOR inhibitor treatment has been shown and has been repeatedly reported with beneficial effects on all these manifestations [28] it can be assumed that all infants and children can have positive effects from the study intervention with sirolimus. It is even hypothesized that long-term positive disease modification can be achieved with mTOR inhibition in TSC [31].

There is a risk for SAEs during treatment with sirolimus and there have been single reports on death in association to sirolimus treatment. Rössler et al. 2021 [32] described SAE in a cohort of children with vascular anomalies and described cases of severe pneumonia. They provide a review on previous deaths during sirolimus treatment, that occurred in young children with kaposiform hemangioendothelioma, which itself is associated with a high mortality. Larger studies assessing the risk-benefit for sirolimus in infants with kaposiform hemangioendothelioma described mainly mild side effects and support sirolimus treatment [33].

In TSC, there have been no reports on death in childhood related to sirolimus treatment so far. Deaths, that occurred during long-term safety studies [29] in mTOR inhibitor treatment with everolimus were not considered to be related to treatment.

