### 1.3.2 Clinical impact

This trial will provide detailed information about benefits and safety of prophylactic mTOR inhibitor treatment in reducing the occurrence and severity of neuropsychologic impairment in TSC. Using a rational, mechanism-based therapeutic strategy, this trial could fundamentally transform the therapeutic management of TSC from a symptomatic to a targeted disease-modifying approach. Eventually, TSC represents a disease, where early intervention can improve long-term performance in school, social and professional life and can serve as a model for targeted mechanism-driven approaches for related neurodevelopmental disorders with and without dysregulated mTOR signaling.

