### 1.3.6 Rational for study medication

Two mTOR inhibitors are available for the treatment of TSC, sirolimus and everolimus. These two medications differ only by one additional ethylester group in everolimus, resulting in differences in their half-lives, solubility, elimination, interindividual tolerability and efficacy. Everolimus is currently approved for the treatment of most TSC-manifestations, including the treatment of SEGAs for all age groups, mostly because Novartis Pharmaceuticals, that developed everolimus, supported the key clinical studies leading to approval by the FDA and EMA [38]. Similar trials with sirolimus failed due to lack of funding and the only approved indication for sirolimus is spontaneous pulmonary lymphangioleiomyomatosis due to proposed somatic mutation of TSC [39]. Direct head-to-head clinical trials comparing both medications in TSC are not available and most authors treating older children and adults, currently prefer everolimus, due to the more robust clinical trial experience [40]. However, sirolimus holds a key advantage over everolimus, in that it is available as oral solution (Rapamune®) facilitating the careful administration of precise doses in neonates and infants. Everolimus, by contrast, is only available as tablet with limited solubility in water, which renders precise dosing difficult and bears higher potential risk of accidental application of inaccurately low or high doses. In addition, sirolimus and everolimus work in a similar fashion, and are considered equally effective and interchangeable by leading TSC experts (reviewed in detail by Franz *et al.* [41]), supported by recent evidence of equal tolerability and efficacy of sirolimus in TSC-related seizures [36, 42]. Furthermore, due to the significant higher cost for everolimus for this publicly funded trial, the investigators favor the use of sirolimus.

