### 4.4 Exclusion Criteria

Subjects presenting with any of the following criteria will not be included in the clinical trial:

1. Has a TSC-associated condition for which mTOR treatment is clinically indicated (i.e. SEGA).
2. Has been treated in the past or is currently being treated at the time of enrolment with systemic mTOR inhibitors (such as rapamycin, sirolimus, or everolimus).
3. Contraindication to study medication. Rapamune® oral solution contains soya oil. Patients allergic to peanut or soya must not take this medicine.
4. Current enrolment, or observation period of competing clinical trials at any time during enrolment in the study.
5. Has a history of significant prematurity, defined as gestational age <30 weeks at the time of delivery, or other significant medical complications at birth or during the neonatal period that other than TSC would convey additional risk of seizures or neurodevelopmental delay (i.e. HIE, severe neonatal infection, major surgery, prolonged ventilatory or other life-saving supportive care or procedures).
6. Abnormal laboratory values at screening (i.e., renal function, liver function, or bone marrow production) that are in the opinion of the investigator clinically significant and may jeopardize the safety of the study patient.
7. Parents / caregivers who are, in the opinion of the investigator, unable to comply with the requirements of the study.

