### 5.6 Concomitant Medication and Therapy

A concomitant medication is any treatment received by the subject concomitantly to the IMP. Therapy of TSC manifestations according to SOC will not be affected by the trial, except for manifestations requiring mTOR inhibitor treatment (e.g. SEGA). Treatments in addition to the study medication should be kept to a minimum during the trial. However, if these are considered necessary for the subject's health and are unlikely to interfere with the IMP, they may be given at the discretion of the investigator, with a stable dose (if possible). Any treatments, which are initiated, continued and/or changed during the trial, must be recorded in the source data and in the eCRF. Medication taken after informed consent is obtained but before the first dose of the study medication will be documented as prior medication. Medication taken after the first dose of the study medication has been administered will be documented as concomitant medication.

|                                                                    |                                              |                                |
|--------------------------------------------------------------------|----------------------------------------------|--------------------------------|
| Clinical Trial Code: PROTECT
EU trial number: 2022-502332-39-00 | Trial Protocol
(Version 06; (01.10.2024)) | Page 64 of 110
CONFIDENTIAL |
|--------------------------------------------------------------------|----------------------------------------------|--------------------------------|

Caregivers will be instructed not to administer any medications (over-the-counter or other products) during the treatment period without prior consultation with the investigator. The investigator should instruct caregivers to inform the study site of any new medications taken by the study participant after initiation of treatment with the study medication.

If concomitant drugs (other than study drug) are administered, these must be recorded in the subject file and in the eCRF, stating:

- The type (preferably the generic name / International Nonproprietary Name (INN), or trade name)
- The route of administration
- The regimen, including dosage schedule, daily dose (if not indicated by the type), and form of application
- The indication (heart, infection, neuro, other)
- The duration

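### The as-treated safety rule in 9.1 regroups a control child only after a prophylactic mTOR inhibitor, so events on an mTOR inhibitor given for a later indication would be counted under standard of care

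*Protocol*

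**What the plan says.** Protocol 9.1 defines the safety set as all randomized children and sets the grouping: "For efficacy analyses the patients will be analysed as allocated, for safety analyses as treated". It then lists when a child changes column for the as-treated analyses. For a child randomized to SOC there is one criterion: "They received prophylactic mTOR inhibitor".

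The adjective is not defined in 9.1. Section 1.3.2 uses it for the trial's own pre-emptive strategy, when it speaks of the "benefits and safety of prophylactic mTOR inhibitor treatment". No other section widens it to an mTOR inhibitor given to treat a manifestation.

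Four other places bear on the point:
- Exclusion 1 in 4.4 removes a child who "Has a TSC-associated condition for which mTOR treatment is clinically indicated (i.e. SEGA"), but only at entry.
- Section 5.6 leaves usual therapy of TSC manifestations unaffected "except for manifestations requiring mTOR inhibitor treatment (e.g. SEGA").
- Section 1.3.6 describes everolimus as approved for most TSC manifestations, "including the treatment of SEGAs for all age groups".
- Section 5.6.3 forbids any other mTOR inhibitor during the study.

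**The concern.** An as-treated table is meant to sort children by the drug they actually received. Toxicity follows exposure, not the reason for the prescription. A rule that moves a control child only when the use was prophylactic leaves a child treated for an indication in the SOC column, together with whatever adverse events the drug causes.

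The error has a direction. It adds drug toxicity to the comparator and so understates the risk of sirolimus, in an age group for which 1.3.8 calls the tolerability data limited. What is at stake is the all-AE, SAE and AESI tables of 9.5.1, mainly the rows with few events.

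**Working it through.** The protocol states no figure for this rule, so the check is first textual and then a calculation of scale.

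**Does the case fall through the rule?**
1. The indication must arise after entry, because exclusion 1 removes those already present. Adverse events are collected until the end-of-trial visit at 25 months of age (8.6.1), so there is time for one to arise.
2. The child stays in the tables. The safety set is all randomized children (9.1). Starting an mTOR inhibitor is not among the reasons for leaving the trial in 7.3 (withdrawal of consent, loss to follow-up, death). The prohibited-medication item in 7.2 concerns stopping the IMP, which a control child does not take.
3. The use was therapeutic, so the only criterion in 9.1 is not met and the child is tabulated under SOC.

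**How many children?** The protocol gives no rate of therapeutic mTOR inhibitor use by 24 months. Assumed range: 0% to 5% of the 30 controls. The chance of at least one such child is 1 − (1 − p)^30:
- p = 0: 0%, none expected
- p = 2%: 45.5%, 30 × 0.02 = 0.6 expected
- p = 5%: 78.5%, 30 × 0.05 = 1.5 expected

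The illustrations below therefore use 0, 1 or 2 children.

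**Rare event, occurring only in the treated control children, after their first dose.** The split adds the child to the exposed denominator and leaves it in the SOC denominator for its earlier time.

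| Treated controls | As written: SOC / sirolimus | Split at first dose: SOC / exposed |
|---|---|---|
| 0 | no change | no change |
| 1 | 1/30 = 3.3% / 0/30 | 0/30 / 1/31 = 3.2% |
| 2 | 2/30 = 6.7% / 0/30 | 0/30 / 2/32 = 6.3% |

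With one child each column moves by about 3 points, and the sign of the difference reverses.

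**Common event.** Assume 25 of 30 sirolimus children, 3 of the other 29 controls, and the one treated control (on drug).
- As written: 25/30 − 4/30 = 83.3 − 13.3 = 70.0 points
- With the split: 26/31 − 3/30 = 83.9 − 10.0 = 73.9 points

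The shift is small beside the difference itself.

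**Why rewording alone is not enough.** Section 9.2 counts events from randomization. Take a control randomized at 2 months and followed to 25 months, which is 23 months. The share of follow-up on drug, if never stopped, is:
- first dose at 8 months: 17/23 = 74%
- first dose at 14 months: 11/23 = 48%
- first dose at 20 months: 5/23 = 22%, so 18/23 = 78% is unexposed

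Leaving the whole child under SOC misplaces the exposed share. Moving the whole child misplaces the unexposed share. For a child first dosed at 20 months, moving it whole would be the larger error.

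**The case against.** The strongest reply is the ban in 5.6.3. Read with it, the exception in 5.6 more naturally marks where the trial restricts usual care than where it plans mTOR treatment for controls. A reader might infer from 5.6 that the protocol expects such treatment; the text does not support that. It recognises the manifestation, and treating it with an mTOR inhibitor would be a deviation. This makes the case rarer but does not close the gap. Section 9.1 already provides for control children who receive an mTOR inhibitor, and then covers only one kind of use.

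A reader might also infer that such a child goes missing from the table of "all adverse events related to the treatment (treated group only") in 9.5.1. That does not hold. Section 8.4.2 has causality assessed only after administration of the IMP and only in relation to it. A control child on everolimus never receives the IMP, so the protocol requires no relatedness judgement for that table, and rewording 9.1 would not supply one.

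Nor can the statement that "about one quarter of individuals will develop SEGA during childhood" serve as the rate here. It would give 0.25 × 30 = 7.5 controls, but over all of childhood. It does not separate out SEGA present at entry, which is excluded, and it counts SEGA whether or not an mTOR inhibitor is used.

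Two further objections stand in part. The split treats the arms unequally, because a sirolimus child who stops early keeps all its later events under sirolimus. It also places one child in two denominators. Both are small costs and can be footnoted. It can also be said that switch time is detail for the statistical analysis plan. That is fair for the split, but not for the criterion, which the protocol itself states and states too narrowly.

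**Conclusion.** The point holds as a minor correction. As worded, 9.1 would tabulate as unexposed any control child given a systemic mTOR inhibitor for an indication arising after entry. The misplacement affects the all-AE, SAE and AESI tables. It is about 3 points per column for a rare event in one child, about 6 to 7 points for two, and nothing if no child is affected.

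These sizes rest on an assumed 0 to 2 affected children among 30 controls and on reading the adjective in its ordinary sense, as 1.3.2 uses it. Several things limit the consequence. The safety tables are descriptive, and 9.3 lists all eCRF data, so the child can be traced. A reader might also fear for the primary comparison, but efficacy is analysed as allocated under a treatment policy strategy and is unaffected.

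**What to change.** In 9.1, replace the criterion for control children with *any systemic mTOR inhibitor, whatever the indication*. Add that, for such a child, adverse events before the first dose count under SOC and events from that dose on count as exposed, with a table footnote that the child appears in both denominators. Since 9.1 also runs the screening characteristics as treated, say in which single column the child is shown there.

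The cost is one reworded bullet and one programming step. Active ingredient, start and stop dates and reason for use are already recorded in the eCRF (6.8). Because the primary analysis does not change, 9.3 allows the change to be made in the statistical analysis plan alone. The two parts belong together, since the new wording without the split could do worse than the present text for a child treated late. The separate 9.1 rule on sirolimus children lost before 6 months is not touched.

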### 9.3 General Considerations

All patient data entered into the eCRF will be listed. Free text will be listed only.

**Patient disposition** will be analysed based on the CONSORT statement, including number patients screened, patients randomized, patients terminating the study prematurely and the number of patients in the analysis populations.

**Screening and disease characteristics** will be analyzed descriptively by treatment group for the SAF using standard summary measures, i.e., number of evaluable observations, arithmetic mean, standard deviation, median, 25 %- and 75 %-quantile, minimum and maximum for continuous data and the number and percentage of patients per category for categorical data.

A statistical analysis plan will be written for the main study by the KKS.

All analyses of the main study will be described in the statistical analysis plan in greater detail. Additional analyses may be added. The accompanying research will not be part of this plan.

In case of any changes to the primary analysis described in this protocol an amendment will be issued pointing out the changes. If necessary, all other changes will be mentioned in the SAP, only.

SAS Version 9.4 or higher will be used for analyses.

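### The one general table of screening and disease characteristics is fixed as treated, so it need not describe the randomised arms that the primary analysis compares

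*Protocol*

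**What the plan says.** Section 9.1 sets the general rule for grouping: "For efficacy analyses the patients will be analysed as allocated, for safety analyses as treated". It then defines the as-treated groups. A child randomised to sirolimus counts as standard of care under either of two conditions: "They are lost to follow-up before 6 months after randomization or" "They never started treatment". A child randomised to standard of care counts as sirolimus under one condition: "They received prophylactic mTOR inhibitor". The first condition has a 6-month window; the rule for control children has no time limit. The section closes with the baseline table: "Screening and disease characteristics will be analysed once by treatment groups as treated".

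Section 9.3 repeats that these characteristics "will be analyzed descriptively by treatment group for the SAF using standard summary measures". This does not bring allocation back. According to Section 9.1 the safety set "comprises all randomized patients and is identical with the" full analysis set, so both sets contain the same children and only the grouping rule can differ. Section 9.1 has already set that rule to as treated.

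Section 9.4 evaluates all randomised children under a treatment policy strategy. The primary comparison is therefore between the allocated arms.

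**The concern.** A baseline table is read to judge whether the groups under comparison started out alike. Here the comparison is by allocation, while the table's columns are assigned partly by what happened later. Reclassified children can create or hide a difference that randomisation did not produce, and the column totals may then disagree with the efficacy tables.

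The loss rule also works in one direction only. Control children lost early stay under standard of care, and sirolimus children lost early are moved there, even if they took the drug first. Early losses from both arms therefore collect in one column. The sirolimus column keeps only allocated children not lost before 6 months, plus any control children who crossed over.

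With 60 children, chance imbalance is plausible. Only the age stratum is built into randomisation (Section 5.1.1) and the primary test (Section 9.4), so readers will want to see the other characteristics for the arms as randomised.

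**Working it through.** **Figures in the plan.** The protocol gives no figure on this point. The nearest is the power in Section 9.9 (above 95% for 30 per group, difference 15, SD 15, two-sided 5%, Mann-Whitney). With the large-sample efficiency 3/π, the effective n per group is 30 × 3/π = 28.65, and power = Φ(15/15 × √(28.65/2) − 1.96) = Φ(1.825) = 96.6%. The stated figure reproduces. It does not depend on how the baseline table is grouped.

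**Inputs.** 30 children per arm (Sections 4.1 and 9.9); 10% missing 24-month values (Section 9.9); the reclassification rules of Section 9.1. The share of missing values that are losses before 6 months is not given, so it is varied below.

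**Column sizes.** If m sirolimus children are reclassified and no control child is, the columns hold 30 − m and 30 + m children.

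**Spurious difference.** Take two arms with exactly equal baseline means. Let the moved children differ from their arm's mean by d SD. The sirolimus column shifts by m·d/(30 − m) one way, and the standard-of-care column by m·d/(30 + m) the other way:

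difference = m·d·[1/(30 − m) + 1/(30 + m)] = 60·m·d/(900 − m²).

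| m | Columns | Difference for d = 1 |
|---|---|---|
| 1 | 29 v 31 | 60/899 = 0.07 SD |
| 2 | 28 v 32 | 120/896 = 0.13 SD |
| 3 | 27 v 33 | 180/891 = 0.20 SD |

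Control children moving the other way can offset or add to this. With m = 3 and one control child moved, the difference for d = 1 is 0.13 SD if that child differs from its arm in the same direction, and 0.27 SD if in the opposite direction.

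**How likely is any move?** Assume a fraction f of the 10% missing values are losses before 6 months, independently between children. The expected number moved is 30 × 0.1f, and the chance of at least one move is 1 − (1 − 0.1f)^30.

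| f (assumed) | Expected moves | Chance of at least one |
|---|---|---|
| 25% | 0.75 | 53% |
| 50% | 1.5 | 79% |
| 100% | 3 | 96% |

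The last row is an upper case: the 10% also covers later drop-out and children missing a 24-month value for other reasons.

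**The case against.** **Baseline features are partly shown by allocated arm.** A reader might infer that nothing in the plan shows whether the randomised arms were comparable. The protocol does not support that. Section 9.5.1 analyses secondary parameters for the full analysis set, with MRI characteristics by group at randomisation. It also covers seizure, EEG, sonography, ECG and echocardiography characteristics by group and time point where applicable, and Table 1 schedules EEG and sonography at screening. Section 9.8 repeats the primary analysis by age group and by infantile spasms at randomisation. Age, the factor the protocol expects to matter, is stratified in both allocation and test. This objection stands and confines the point to the general characteristics table.

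**Few children should move.** Treatment starts on the day of randomisation (Section 5.1.1), with the first dose at the centre (Section 5.4), so never starting should be rare. Other mTOR inhibitors are not allowed (Section 5.6.3). Loss to follow-up (Section 7.3.2) is separate from withdrawal of consent (Section 7.3.1), and stopping treatment moves nobody. This also stands, and it keeps the size modest.

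**A large false imbalance is an extreme case.** One can construct an example: infantile spasms in 6/30 of each arm, and three affected sirolimus children moved, gives 3/27 (11%) v 9/33 (27%), a gap of 16 points. It treats the whole missing-value rate as early loss and assumes a prevalence that the protocol does not state. If loss is unrelated to spasms, the chance that all three moved children are affected is C(6,3)/C(30,3) = 20/4060, about 0.5%. It should not be quoted as the expected size.

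**The analysis plan could add a table.** Section 9.3 lets the statistical analysis plan add analyses. That makes the remedy easy, but the protocol has not left the grouping open: it specifies a single table and specifies it as treated.

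**Conclusion.** The point holds as a presentation defect. The only general table of screening and disease characteristics is grouped by rules that use post-randomisation events, while the primary comparison is by allocation. The table therefore need not describe the randomised arms.

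If 1 to 3 sirolimus children are reclassified and no control child is, the columns run from 29 v 31 to 27 v 33. The spurious difference is about 0.07 to 0.20 SD for each SD by which the moved children differ. Both the number moved and how far they differ are assumptions. If nobody is reclassified, the two groupings coincide and the problem disappears.

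A reader might go further and infer that the primary result is biased. The documents do not support that: the primary test uses the allocated arms, and its significance level and power do not change.

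**What to change.** In Section 9.1, replace the closing sentence on the baseline table with: *Screening and disease characteristics will be presented by allocated arm for all randomised children (FAS).* Change Section 9.3 to name the same set and grouping. Add an as-treated version beside the safety tables only if the two groupings differ.

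The cost is one sentence and one matching edit, with no new data and no effect on sample size. Because the primary analysis is untouched, Section 9.3 allows the change to be recorded in the statistical analysis plan alone, with the protocol text corrected when it is next amended.
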